### Sample size

There are no previous studies with comparable analysis, allowing for a formal sample size calculation. Therefore, we have taken the difference in hormone level as the starting point for a sample size calculation. Based on an expected difference of 20% in hormone level changes between lean and obese patients (decrease in hormone levels of 70% in lean, and 50% in obese after BSO), using a 90% power and alpha 0.05, 154 patients are required for the primary objective of this study [29]. We have chosen to include 160 women, 80 obese and 80 non-obese. The gap in BMI between the 2 groups (7/10 BMI points) increases the likelihood to obtain significant differences in hormone- and inflammation marker levels.

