### Data collection schedule (Fig 3)

**Fig 3 pone.0276516.g003:**
[figure not shown]
Schematic display of content and timepoints (T) for data collection during the study period. Three time points for patients with benign disease (T1-T3) and four time points (T1-T4) for patients with endometrial cancer (EC).

At three (women with benign diagnoses) or four (women with EC) different time points data will be collected from the subjects.

At timepoint 1 (T1), a physical examination is conducted where hip and waist circumference are measured and patient variables including age, height, weight, BMI, history, cumulative illness rating scale (CIRS) and menopausal status collected. Furthermore, routine abdominal CT imaging will be performed in all patients. Finally, patients are requested to answer a validated questionnaire, the Green climacteric scale enquiring into presence of menopausal symptoms, and are asked to answer three questions on their physical activity level.

At timepoint 2 (T2) subjects will undergo the clinically indicated surgical procedure. At start of surgery, a fasting blood draw will be obtained to measure oestrogen levels and systemic inflammation markers. During surgery subcutaneous adipose tissue and visceral adipose tissue (fat apron and intestinal epiploic fat) as well as tumour (where applicable) will be collected, and snap frozen.

At timepoint 3 (T3) 4 to 6 weeks postoperatively, another fasting blood draw is obtained for measurement of oestrogen levels and systemic inflammation markers. In case of a recent infection the blood draw will be postponed until 10 days after the end of the infection. In case of adjuvant therapy, the postoperative blood draw will be performed latest at start of the adjuvant therapy. Finally, subjects will be asked to fill in the Green climacteric scale questionnaire a second time.

For subjects with the diagnosis of EC clinical follow-up data will be collected during 3 years (T4).

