### Stratification

We strive to include a safety margin of 5–10% per stratum to allow for missing data. In both cohorts, due to a short preoperative waiting list (<4 weeks) it is not expected any patients are included whose data or tissue is not subsequently used. For this study, we can optimally compare the included participants using our 20/20/20/20 distribution. Using a population-based inclusion, we would likely have too low numbers in some groups to allow for meaningful analyses. However, as a consequence the external validity is somewhat reduced.

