### Statistical analysis

Variables will be analysed quantitatively (CT derived markers, hormones and inflammatory markers) or qualitatively (menopausal symptoms) and stratified by menopausal status and BMI. Comparison of characteristics and study variables will be performed using Chi squared tests (categorical data) and Mann Whitney U test or student t-test (continuous variables, depending on normality of distribution). Correlations will be assessed using Spearman’s rank correlation. Study-related, the oncological patients will be followed for three years for disease recurrence and/or disease-related death. Additionally, correlations between inflammatory markers in adipose tissue and circulating oestrogen levels after treatment and outcome are observed.

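### Relating markers to three-year recurrence or disease-related death by correlation ignores event time, and can attenuate the association if women are lost or die of other causes

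*Protocol article*

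**What the plan says.** Three sentences of the Protocol article, Statistical analysis, bear on this, in this order:

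- "Correlations will be assessed using Spearman’s rank correlation". This follows the chi-squared, Mann-Whitney U and t-tests, and completes the list of methods.
- "Study-related, the oncological patients will be followed for three years for disease recurrence and/or disease-related death".
- As an addition, "correlations between inflammatory markers in adipose tissue and circulating oestrogen levels after treatment and outcome are observed".

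The Data collection schedule gives the same three years of clinical follow-up (T4), for subjects with EC only. The Objective/aim section lists neither recurrence nor death among the primary or secondary objectives. The article gives no event rate, effect size or power for this outcome.

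**The concern.** Recurrence or disease-related death accrues over three years, so each woman contributes a time at risk as well as a yes or no. Because only disease-related death counts, death from any other cause is a competing event by definition. A rank correlation with event status cannot represent either feature: a woman lost at month 6, or dead from another cause, is either counted as event-free or dropped.

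The article's own background makes marker-related loss plausible. The Introduction ties obesity to diabetes and cardiovascular disease, and also to chronic inflammation and to oestrogen production in fat. Half the cohort is obese by design, so the markers to be related to outcome may also track other-cause death. What is at stake is the size and interpretation of the reported marker–outcome relation.

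**Working it through.** **Inputs.** From the article: 160 women ("We have chosen to include 160 women, 80 obese and 80 non-obese"), three-year follow-up, and a "we can optimally compare the included participants using our 20/20/20/20 distribution". Reading the last as four cells of 20 per BMI group, two of them cases, gives 2 × 2 × 20 = 80 cases. This is an upper bound for EC, because the Participants section counts atypical hyperplasia among the cases. The article states no figure for this outcome that could be reproduced. All event, loss and other-cause death rates below are assumptions.

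**1. Ceiling on rho with complete follow-up.** Scale marker ranks to 0–1 (variance 1/12). Event status has variance p(1−p). If every event falls in the top fraction p of the marker (a perfect predictor), the covariance is p(1−p)/2. Hence

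max rho = [p(1−p)/2] / √[p(1−p)/12] = √(3p(1−p)).

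- p = 5%: √0.1425 = 0.38
- p = 10%: √0.27 = 0.52
- p = 15%: √0.3825 = 0.62

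**2. Effect of losses.** Simulation with 80 cases, a standard-normal marker, exponential event times, administrative end at 3 years and 1,500 runs per setting. Women lost or dead of other causes are counted as event-free for Spearman and censored for Cox. In the last column other-cause death has a hazard ratio (HR) of 2 per SD of the marker, and its 10% applies at the average marker value. Cells show mean rho with full ascertainment → mean rho observed (relative fall, from rounded means).

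| Incidence | HR per SD | 10% lost, 5% other death, unrelated | 20% lost, 10% other death, unrelated | 20% lost, 10% other death, death related |
|---|---|---|---|---|
| 10% | 1.5 | 0.128→0.123 (3.9%) | 0.122→0.112 (8.2%) | 0.120→0.093 (22.5%) |
| 10% | 2.0 | 0.196→0.190 (3.1%) | 0.200→0.184 (8.0%) | 0.198→0.163 (17.7%) |
| 20% | 1.5 | 0.171→0.164 (4.1%) | 0.170→0.156 (8.2%) | 0.166→0.131 (21.1%) |
| 20% | 2.0 | 0.275→0.264 (4.0%) | 0.275→0.253 (8.0%) | 0.277→0.232 (16.2%) |

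With no loss the two values coincide (for example 0.271 and 0.271 at HR 2.0 and 20% incidence).

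**3. Power, Cox versus Spearman.**

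- Complete follow-up, 10% incidence: HR 1.5, 19.6% v 18.0%; HR 2.0, 47.5% v 45.5%.
- Complete follow-up, 20% incidence: HR 1.5, 35.4% v 33.6%; HR 2.0, 72.9% v 70.1%.
- HR 2.0, 20% incidence, 20% lost and 10% other death: 67.7% v 63.4% if unrelated to the marker, 64.9% v 55.8% if other-cause death is related.

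At HR 2.0 and 20% incidence, the mean Cox log HR was 0.723 with complete follow-up and 0.722 with marker-related other-cause death (true value ln 2 = 0.693), so it did not shrink as rho did.

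**4. No true association.** Mean rho was never further from zero than −0.014, and Spearman's rejection rate was 3.5–6.8%. In the settings with loss it was 3.5–5.5%.

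**5. Precision.** Mean event counts ran from about 6 to 16. With 8 events, the 95% interval for an HR per SD spans a factor of exp(1.96/√8) = 2.0 either way.

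**The case against.** The strongest reply is that the method is pieced together. The Spearman sentence precedes any mention of follow-up, the closing sentence does not repeat the name, outcome is not defined as a status or a time, and correlation may loosely mean association. On that reading only a survival method is unspecified, which a condensed article may leave to the full plan. The ambiguity is real. But the same paragraph uses the same word for this outcome and offers one method for it, and no listed method handles event time, censoring or competing death. As written, the text points to an ill-suited method; it is not merely silent.

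Several stronger readings are tempting, and the documents do not support them:

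- *The oncological result will be attenuated.* Follow-up is a fixed three years. If it is complete there is no attenuation, and only about 2–3 points of power are lost. The article does not say how lost women will be counted, and its allowance ("We strive to include a safety margin of 5–10% per stratum to allow for missing data") is not specific to the three-year follow-up.
- *False positives are inflated.* The simulation shows no material inflation.
- *Rho cannot be compared between markers.* In the same women the ceiling is the same for every marker. With a binary outcome rho is approximately (2·AUC − 1)·√(3p(1−p)), so it does carry discrimination. The ceiling is a matter of scale; it impairs comparison across studies with different event rates.

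It also stands that the analysis is additional, and that scarce events limit it more than the choice of method does. A Cox model does not cure that.

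**Conclusion.** The point holds in conditional form, at low severity. Correlation is the stated approach for an outcome that accrues over time. It ignores event time and cannot handle loss or other-cause death. Attenuation is possible but not certain: none with complete follow-up, about 3–8% with losses unrelated to the marker, and about 16–22% if other-cause death rises with the marker. Only that direction of relation was simulated. The dependence of rho on the event rate remains even with complete follow-up, so it is not a prognostic effect size that can be carried across studies.

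These sizes rest on 80 cases and on assumed incidence, loss and hazard ratios, none of which the article gives. No primary or secondary objective is touched.

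**What to change.** For this outcome, replace correlation with a time-to-event analysis in women with EC:

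- Endpoint: time from surgery to first recurrence or disease-related death, censored at last contact or 3 years.
- Other-cause death as a competing event.
- Report cumulative incidence and cause-specific hazard ratios with 95% confidence intervals.
- Limit it to a few named markers, because few events are expected, and label it exploratory.
- Keep Spearman's correlation for relations between markers.

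A penalised fit for sparse events and the exact number of markers are preferences, not required changes.

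The cost is analysis wording, plus making sure that the dates of recurrence, death (with cause) and last contact are recorded in the T4 follow-up already planned. The downside is that fewer markers are tested against outcome. Sample size and the planned visits do not change.

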## Discussion

The goal of this prospective cohort study is to explore the differences between obese and non-obese women as well as the importance of fat distribution in relation to EC. This study set up, with two academic hospitals and two big teaching hospitals, is well suited to better understand the relation between obesity and endometrial cancer. Because we will include a big range of women with different BMI, menopausal status and pathology, we think this is the perfect setup to generate those much needed knowledge.

A strength of this study is that the big difference in BMI between the two groups will optimally allow for finding any existing obesity-related differences in hormone levels and inflammatory markers. A possible limitation of the resulting BMI gap may thus be the translation of this effect on to the intermediate population. When looking at prevalence of obesity in the Netherlands in 2017, we see that 15.7% of the women were obese, but only 4% had a BMI above 35kg/m2 [33]. However, data from the Netherlands Comprehensive Cancer Organisation specific for women with endometrium carcinoma shows a mean BMI of 30.2 (SD 7.0) kg.m^2^ in 2019 in this population. Of the 2085 EC patients in 2019, 23.4% had a BMI between 30–39.9 and 23.4% a BMI between 25–29.9. It has to be noted that in this dataset BMI was unknown in 35% of the patients [34]. Therefore it is most likely that if we find differences in our population, and further research should confirm this also for the intermediate BMI group (BMI 25–35).

Another strength of this study is that we are able to compare low cost fat distribution measures such as waist-hip circumference with the more accurate fat distribution quantifications based on CT-scan, representing the golden standard for measuring subcutaneous/visceral adipose tissue. Because routine CT imaging, due to cost and radiation is not suitable for application in a healthy general population, waist-hip measurement may represent an easy and attractive alternative to CT if this is correlated to the CT morphometric markers.

Further, by including equally pre/ perimenopausal and postmenopausal women we can pin-point what effect the actual obesity has on the sex-steroid levels. An expected limitations will be that most women will be around menopausal age, because BSO may in specific very low risk situations be refrained from in women <45 years of age, balancing the risks of EC recurrence and iatrogenic menopause and is contra-indicated in women with a benign diagnoses.

Previous studies have found several clues for a relationship between obesity and endometrial cancer [5–7, 14]. We expect that our study will contribute to pinpoint the exact differences between ‘healthy obesity’ and ‘unhealthy obesity’ and will help to identify patients that are more at risk of developing cancer (or possibly suffer from other related problems such as cardiovascular problems e.g.).

Finally, our study will be able to relate the occurrence of menopausal complaints to BMI and fat distribution, which has not been previously addressed in in existing literature.

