### Objective/aim

The aim of this study is to compare hormone levels and inflammatory markers after BSO in obese and non-obese patients. Secondary objectives are to compare the effect of fat distribution and diagnosis (benign vs. endometrial cancer) on changes in hormone levels and inflammatory markers after BSO in obese and non-obese patients, and to compare the effect of BSO on menopausal complaints. We hypothesize that obese post-menopausal women will still have relatively high circulating concentration of oestrogen, especially women with a high subcutaneous fat percentage.

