### Participants (Fig 2)

**Fig 2 pone.0276516.g002:**
[figure not shown]
Schematic display of participants. Total number of participants is 160 women.

In total 160 patients will be included, of which 80 patients with a normal BMI between 18–25 kg/m2 and 80 obese patients with BMI ≥35 kg/m2 (WHO obesity class 2). In both these groups an even number of peri-/premenopausal women and postmenopausal women are included, and women with endometrial cancer (EC) and/or atypical endometrial hyperplasia; cases, and women with a benign adnexal pathology (including but not limited to adnexal enlargement/abnormality); controls will be included. Patients will be included pre-operatively. In case of a final diagnosis being ovarian malignancy, this participant will be excluded and a patient with a benign diagnosis included instead.

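### Age may be mixed with diagnosis in the benign versus endometrial cancer contrast among pre/perimenopausal women, and the stated tests cannot separate the two

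*Protocol article*

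**What the plan says.** All references are to the Protocol article.

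- **Objective/aim** sets the contrast: "Secondary objectives are to compare the effect of fat distribution and diagnosis (benign vs. endometrial cancer) on changes in hormone levels".
- **Participants** defines the comparison group: "women with a benign adnexal pathology (including but not limited to adnexal enlargement/abnormality); controls will be included". It balances menopausal status within each BMI group: "In both these groups an even number of peri-/premenopausal women and postmenopausal women are included". Pre- and perimenopausal women form one category. No age limit or age matching is stated.
- **Stratification** refers to comparing participants "using our 20/20/20/20 distribution".
- **Data collection schedule** lists age among the variables recorded at T1.
- **Statistical analysis** says variables are "stratified by menopausal status and BMI" and names, for continuous variables, "Mann Whitney U test or student t-test (continuous variables, depending on normality of distribution". Age does not appear.
- **Discussion** says BSO may be omitted in certain very low-risk situations "in women <45 years of age, balancing the risks of EC recurrence and iatrogenic menopause and is contra-indicated in women with a benign diagnoses". The one consequence drawn is this: "An expected limitations will be that most women will be around menopausal age".

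**The concern.** The Discussion describes access to BSO that differs by diagnosis below age 45. A woman with EC will usually have the operation unless her risk is very low. A woman with benign disease will generally not have it. Since BSO is the route into the study, the two diagnosis groups can differ in age by design.

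Stratifying by menopausal status removes the age difference between strata. It does not remove one inside the pre/perimenopausal stratum, which is where women under 45 will mostly be. The Introduction says the ovaries are the main oestrogen source before menopause, so the fall after BSO may plausibly depend on how far a woman is from menopause. If it does, and if cases are younger, part of an observed benign–EC difference in hormone change would be an age difference. A true difference in the opposite direction could be hidden in the same way. The article mentions the age rule as a limit on age range but does not carry it to this contrast.

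**Working it through.** The plan gives no sample size, age distribution or age effect for this contrast, so there is no figure of its own to reproduce. The steps below show what would follow under stated assumptions.

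**1. Reading the age clause.** The part about benign disease carries no age limit of its own. If it covered benign women of all ages, the control group required under Participants could not exist. The under-45 reading is the workable one and is used here.

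**2. Cell sizes.** Two BMI groups of 80, each split 20/20/20/20, give 8 × 20 = 160. Taking the four cells as menopausal status by diagnosis is a reading of the text. It gives 20 cases versus 20 controls per BMI group in the pre/perimenopausal stratum, or 40 versus 40 pooled over BMI. The stated stratification implies the 20 versus 20 comparison.

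**3. Spurious difference.** Let p be the share of cases under 45 and d the extra fall under 45 in SD units, with no controls under 45 and no true effect of diagnosis. The spurious difference is p × d.
- Low end: 0.10 × 0.5 = 0.05 SD.
- High end: 0.30 × 1 = 0.30 SD.

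Both p and d are assumptions.

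**4. False-positive rate of the unadjusted t-test** (nominal 5%, normal outcome, 100,000 simulated trials per setting):

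| p | d | 20 vs 20 | 40 vs 40 |
|---|---|---|---|
| 0.1 | 0.5 | 5.3% | 5.5% |
| 0.1 | 1 | 6.0% | 7.2% |
| 0.2 | 0.5 | 6.1% | 7.2% |
| 0.2 | 1 | 8.9% | 13.5% |
| 0.3 | 0.5 | 7.5% | 9.9% |
| 0.3 | 1 | 14.1% | 24.3% |

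The Mann-Whitney test gives 5.3–13.0% and 5.6–21.8%. If 5% of controls are also under 45, the t-test gives 5.1–11.2% and 5.1–17.7%.

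**5. Does age adjustment help?** Pooled 40 versus 40 was simulated with 6,000 runs in each of 24 settings: three values of p, two of d, an age effect that is linear or a step at 45, and a BMI effect of 0 or −0.5 SD.
- Full stratum, regression on diagnosis, BMI group and age: 4.7–8.5%. The worst case is the step with p = 0.3 and d = 1, where a bias of 0.13 SD remains because the linear age term extrapolates to ages with no controls.
- Restricted to women aged 45 or older, same model: 4.5–5.6%, bias at most 0.01 SD.

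These runs used one common effect of diagnosis. The BMI-specific version recommended under the fix was not simulated separately.

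**6. Precision lost by restriction** (80% power, two-sided 5%). If 10–30% of cases are under 45, 36 to 28 of 40 cases remain. The pooled detectable difference rises from 0.63 to 0.65–0.70 SD. Within one BMI group it is 0.91 SD for 20 versus 20. Scaling by the standard error:
- 18 of 20 cases left: 0.91 × √[(1/18 + 1/20)/(2/20)] ≈ 0.93 SD.
- 14 of 20 cases left: 0.91 × √[(1/14 + 1/20)/(2/20)] ≈ 1.00 SD.

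**The case against.** **This is a condensed article, and covariates may be left to a fuller plan.** That is partly right. If an unseen plan already adjusts for age, the sponsor need only confirm it. But the article does name its tests and its stratifiers, and it describes the age-dependent selection itself. Applied as written, those tests leave that selection uncorrected. The planned comparison of characteristics could show an age imbalance, but showing it does not remove it.

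**The imbalance may be small.** This stands. The authors expect most women to be near menopausal age, and very low-risk EC patients under 45 may also be spared BSO. The Exclusion criteria remove women expected to be offered HRT immediately after surgery, which may thin out younger women further, although the article does not say from which diagnosis group. No passage supports any particular share of cases under 45.

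**No age effect within the stratum is documented.** This also stands. The Introduction contrasts women before and after menopause, not younger with older premenopausal women.

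**A stronger remedy might seem to follow.** A reader might infer that the conclusion in this stratum should rest on women aged 45 or older alone, or that one regression pooled over BMI should replace the stratified tests. The documents do not support either. Restriction discards cases to counter a bias of unknown size. The objective asks about diagnosis in obese and non-obese patients, and the analysis is stratified by BMI, so a single pooled effect would drop contrasts that the plan calls for.

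**Conclusion.** The point holds as a possible confounding by age of one secondary contrast, in one stratum. It rests on the under-45 reading of the Discussion and on two quantities that the documents do not give: how many more cases than controls are under 45, and how much larger their hormone fall is. Under the assumed ranges, the comparison that the plan implies has a false-positive rate of about 5–14%, or about 6–9% if 20% of cases are under 45. The figure of 24% belongs only to the most adverse setting of a pooled test, which the stated BMI stratification does not describe.

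A reader might infer that the benign–EC result will be biased, or that the main result of the study is in doubt. Neither follows. The documents establish unequal access to BSO by age, not an actual age gap or an age effect, and the rule separates diagnoses rather than BMI groups. The change is worth making as a nearly free improvement.

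**What to change.** For the benign–EC contrast in hormone change among pre/perimenopausal women:

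1. Replace the unadjusted test with a regression on diagnosis and age at T1. Either include BMI group and a diagnosis-by-BMI term, or fit the model within each BMI group, so that the BMI-specific contrasts remain. Analyse change on the log scale if it is skewed.
2. Report the age distribution by diagnosis in this stratum.
3. Because there may be few or no controls under 45, add an age-adjusted sensitivity analysis restricted to women aged 45 or older. If it differs from the full-stratum result, state the conclusion with caution.

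The cost is one covariate that is already collected and one extra sensitivity analysis with somewhat fewer cases, hence the modest loss of precision shown above. Restriction to 45 or older does not separate pre- from perimenopausal women. Recruitment, surgery and the primary obese versus non-obese comparison stay unchanged.
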